## Abstract

**Background:**

Radiotherapy is one of the most important treatments of primary and metastatic brain tumors. Unfortunately, it can involve moderate to severe complications among which leukoencephalopathy is very frequent and implies cognitive deficits such as memory, attention and executive dysfunctions. However, the incidence of this complication is not well established and the risk factors and process are poorly understood. The main objective of the study is to improve knowledge on radio-induced leukoencephalopathy based on pluridisciplinar approaches combining cognitive, biologic, imagery and dosimetric investigations.

**Method/Design:**

The EpiBrainRad study is a prospective cohort study including newly diagnosed high grade gliomas patients treated by radiotherapy and concomitant-adjuvant temozolomide chemotherapy. Patients are included between their surgery and first day of radio-chemotherapy, and the follow-up lasts for 3 years after treatment. Cognitive functioning assessments, specific blood biomarkers measures and magnetic resonance imagery are performed at different moment during the follow-up, and a specific dosimetric assessment of organs involved in the beam fields is performed. Firstly, leukoencephalopathy incidence rate will be estimated in this population. Secondly, correlations between cognitive impairments and dosimetry, biomarkers ranges and anomalies on imagery will be analyzed in order to better understand the onset and evolution of cognitive decrement associated with radiotherapy. Furthermore, a new cognitive test, quickly and easily performed, will be studied to determine its sensibility to detect leukoencephalopathy decrement.

**Discussion:**

With an original multidisciplinary approach, the EpiBrainRad study aims to improve knowledge on radio-induced leukoencephalopathy in order to improve its early diagnosis and prevention. The main challenge is to preserve quality-of-life after cancer treatments which imply to study the incidence of radiation-induced complications and their associated risk factors.

**Trial Registration:**

NCT02544178

## Background

Radiotherapy is one of the most important treatments of metastatic and primary brain tumors of which 60 % are high grade glioblastomas. With the recent development of modern irradiation techniques, survival of patients has increased and mid- to long-term side effects became more visible, such as neurologic complications [1]. Among these complications, leukoencephalopathy seems to be the most frequent. It is characterized by a progressive and diffuse demyelination, an axonal loss and vascular lesions [2]. Consequences of leukoencephalopathy involve cognitive deficits which dramatically reduce the patient’s quality-of-life [3–5]. Thus, since the last few years, the neuropsychological status represents an important issue in clinical trials as well as in individual outcomes [6]. Long-term memory, information speed processing, attention and executive functions are recognized to be the most sensitive functions to be affected by radiations [2, 7–10]. However, there is no consensus to describe the main evolution of cognitive decrement following radiotherapy because of important differences in studies’ protocols (assessment time, decrement definitions, material). The radiation-induced leukoencephalopathy incidence is thus difficult to estimate precisely and varies from 30 to 50 % [10, 11] according to the length of follow-up. Moreover, available studies are often retrospective which may induce bias and based on small samples which limits statistical robustness of results.

Although several risk factors of neurotoxic complication have been identified such as patient’s age, tumor location, total dose of radiation, fractionation, field size [2, 9, 12], the pathophysiology of radiation-induced neurotoxicity is still poorly understood. It could involve inflammation, blood barrier disruption, vascular lesion, demyelination, radio-necrosis and edema [2, 9]. Until now, it is impossible to precisely estimate at individual level the risk for a patient to develop this neurotoxic complication [13, 14]. Some individual risk factor such as cardio-vascular diseases (hypertension, diabetes), smoking, old age [15, 16] seem implicated in leukoencephalopathy. Assessment of the impact of both individual risk factors and treatment toxicity requires to study a large group of patient with prospective collection of accurate data and follow-up.

From a biological point of view, biological mechanisms of the initiation and progression of cognitive impairements is not well known. However, specific biomarkers predictive of the cognitive impairments in this population would help in screening patients at risk of neurotoxicity. Currently, biomarkers of neurotoxicity have been poorly studied. Thus, several markers deserve to be explored such as the S-100B protein known to be a marker of traumatic cerebral lesion, neurodegenerative diseases and aggressive gliomas [17], specific isoprostanes (as 8,12-*iso*-iPF_2α_-VI) implicated in the oxidative/nitrate stress in neurodegenerative diseases [18] and homocystein which plasma concentration has been associated with poor memory performances in old individuals [19]. Furthermore, new biomarkers seems to be potentially very interesting. Indeed, micro RNA and microparticules have been identified as potential biomarkers of neurological defects [20, 21]. Then the strategy proposed is to test classical and new biomarkers in order to individualize those, which could be accurate for the screening of patients at risk of cognitive impairments.

At last, assessment of cognitive impairment is difficult because the exploration of cognitive side effects is not systematic and often depends on patients’ complaints and clinicians’ sensibility to this aspect. A formal neuropsychological assessment can’t be performed in routine, as often as it should be for an adapted follow-up of brain tumor patients. Indeed, it is time consuming, needs expert professionals and validated material, and consequently it is not easily implemented in most medical center. A new tool for exploration of cognitive deficits is the *Computerized Speed Cognitive Test* (Legal deposit: IDDN.FR.001.180018.000.S.P.2014.000.31230) (CSCT) [22]. The CSCT was first developed to assess information speed processing in multiple sclerosis. Because it presents a low learning-effect and focuses on a cognitive characteristic often impaired in neuro-oncologic population, it could be used to detect a cognitive deterioration during repeated medical visits, and thus be used as an alarm to start a more extensive formal assessment. Then, it is suitable for the follow-up of a cohort of patients treated for brain tumor and allows to give quick and reliable information on cognitive impairment, compatible with the usual clinical follow-up of the patients.

### Objectives

The purpose of the EpiBrainRad study is to establish a cohort of patients treated with radiotherapy for a high grade glioma.

The main objective is to estimate the cognitive impairment incidence related to radio-induced leukoencephalopathy in this population.

Secondary objectives are:To study the impact of associated risk factors on leukoencephalopathy development, including individual factors and treatment.Biologic markers of neurologic degradation will be studied to evaluate the correlations between cognitive impairments and biological abnormalities.Specific organs dosimetry (such as hippocampus, temporal lobes, corpus callosum, peri-ventricular white matter, posterior fossa) correlated with radiologic abnormalities on magnetic resonance imagery (MRI) and clinical symptoms will be analyzed to better understand the evolution of radio-induced leukoencephalopathy.Finally, the assessment of the sensibility and specificity of a quick cognitive test, *the Computerised Speed Cognitive Test* [22], to detect a cognitive decrement during the follow up of the patients.

## Methods/Design

### Study design and patient selection

The EpiBrainRad study is an observational prospective cohort. Patients’ recruitment takes place at *Hôpital de la Pitié-Salpêtrière (Paris, France)* and *Centre de Lutte Contre le Cancer Paul Strauss (Strasbourg, France)* for 2 years and each patient is followed during 3 years. The cohort includes newly-diagnosed adults treated for a high grade glioma according to the procedure described by Stupp et al. [23]. According to patient’s age, the radiotherapy regiment can be modified to 40 gy in 15 fractions to ensure a better tolerance in elders [24]. Inclusion and exclusion criteria are listed in Table 1. Data are prospectively including clinical features, MRI images and results, blood samples, dosimetry and cognitive assessments during the usual medical follow-up.

**Table 1 Tab1:** Inclusion and exclusion criteria

Inclusion criteria	Exclusion criteria
• Newly diagnosed grade III or IV glioma • Age ≥ 18 • Treated by radiotherapy and concomitant-adjuvant Tomozolomide as described by Stupp et al. [23] or with an abbreviated course of radiotherapy in elders patients [24] • Treatment and clinical follow-up performed at *Hôpital de la Pitié-Salpêtrière (Paris, France)* or *Centre de lute contre le cancer Paul Strauss (Strasbourg, France)*	• History of other CNS tumor • History of neurologic and/or psychiatric disease involving cognitive impairments (TBI, Stroke, mood and personality disorders…) • Insufficient understanding of French language

### Ethical approval

This study has received ethical approval from the *Comité de Protection de la Personne de Paris VI Ile de France* in December 2014 (ID: CPP/132-14) and from National Agency for Medical and Health products Safety (Reference: 2014-A01697-40). The Clinical Trial Registration Information is available at http://www.clinicaltrials.gov (Unique identifier NCT02544178). Participants enrolled in the study provide their written informed consent.

### Study endpoints

The primary endpoint is the reduction in performance on cognitive tests defined as follows: After exclusion of local recurrence, decreased detailed neuropsychological assessment score compared to the patient's baseline score before radiotherapy for at least 2 cognitive domains.

Secondary endpoints are:Differences in biomarkers’ concentration between the measurements before RT and: at the end of the RT, RT + 4 weeks, RT + 12 months and RT + 36 months.Changes in MRI images compared to the baseline imaging.Correlations between dosimetry, cognitive decay and MRI abnormalities onset after RT.

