Self-reported Scales	
Mood	Anxiety questionnaire of Goldberg [49]
	Center for Epidemiologic Study Depression Scale [50]
Fatigue	FACIT Fatigue Scale [51]
Memory complaint	MacNair and Khan questionnaire [52, 53]
Quality-of-life	EORTC QLQ-C30 [54]
	EORTC QLQ-BN20 [55]
Care-giver-reported Scales	
Dysexecutive syndrome	ISDC [45, 46]
Autonomy	EIADL [56]

Baseline and trimensual MRI during the medical follow-up are used for extra analysis in order to study white matter abnormalities and cortical atrophy. Moreover, tumor response or progression will be assessed by the Response Assessment in Radio-Oncology working group (RANO) Criteria [25]. The white matter lesion quantification will follow the procedure described by Wahlund et al. [26] using a 4 points scale (0: no lesion; 1: focal lesions; 2: beginning confluence of lesion; 3: diffuse involvement of the entire region). The cortical atrophy quantification will follow the procedure described by Pasquier et al. [27] using a 4 points scale (0: absence of atrophy; 1: mild atrophy; 2: moderate atrophy; 3: severe atrophy). White matter lesion and cortical atrophy is assessed for all key region listed in Table 3. A double blind lecture of the MRI will be done in order to quantify these anomalies. Radiological outcomes will then be correlated with cognitive outcomes.

**Table 3 Tab3:** Regions prospectively explored on MRI and dosimetric analysis

Key regions investigated		
	MRI	Dosimetry
Frontal lobes	*	*
Temporal lobes	*	*
Parietal lobes	*	
Occipital lobes	*	
Cerebellum	*	*
Basal ganglia	*	
Brain Stem	*	*
Hippocampus		*
Corpus Callosum		*
Periventricular white matter		*

* anatomical region investigated

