### Statistical analysis

#### Sample size consideration

The main objective being to estimate the incidence of occurrence of neurological complications in the cohort, with an expected proportion P varying from 0.2 to 0.5, for a confidence level of 95 %, with alpha risk of 5 %, the number of subjects to be included varies between 246 and 384. Given the risk of relatively early death related to the disease, the inclusion of 400 patients will provide good statistical power for this purpose.

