#### Analysis of evaluation criteria

Based on primary endpoint definition, the estimate of the incidence of cognitive impairment related to radio-induced leukoencephalopathy in our cohort will be made.

An analysis of the dose–response relationship between radiation dose absorbed by different brain structures and cognitive abnormalities observed after radiotherapy will be made using a multivariate Cox model taking into account the delivered dose to the organ of interest and the time occurrence of cognitive complications. An adjustment on risk factors for cognitive complications will be achieved. Similarly for patients with cognitive impairment before radiotherapy, an analysis of potential associated risk factors will be carried out with the use of a multivariate model.

Secondary judgments criteria, including changes in MRI images relative to the reference imaging and changes in series of biological markers between measurements before RT, 4 weeks, 12 month and 36 months after RT, will be analyzed by parametric distribution comparison tests (Z) or nonparametric if needed (Wilcoxon tests).

In addition, an analysis will be conducted of the sensitivity and specificity of the CSCT to demonstrate cognitive impairment by comparing the CSCT performed before radiotherapy and detailed neuropsychological assessment (gold standard) achieved at the same time. More, CSCT decay during follow-up will be analyzed by comparing its results to formal assessment during years after treatment, to study its sensibility in detecting cognitive decrement after radiotherapy.

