One other important goal of our project is to improve the detection of cognitive defects at early stage. Current formal assessment of cognitive status lasts between 1 and 2 h or more, and cannot be performed as often as needed in this population because of an important learning-effect. The *Compurterised Speed Cognitive Test (CSCT)* is a quick cognitive assessment tool validated in a population of patients presenting multiple sclerosis. The CSCT just need few minutes to be performed and appears to be a potential useful tool in the patient follow-up [36]. This test use in the neuro-oncologic context could importantly improve the detection of cognitive impairments and decrement. Our study will help to validate its use in our population by comparing the CSCT to a more complete battery at baseline time before radiotherapy and during the follow-up after treatment. Several biomarkers of neurotoxicity will be also tested in our population in order to try to individualize prognostic biomarkers of leukoencephalopathy.

Prospective methodology of data collection and the choice of a homogenous population will allow us to analyze precisely the selected outcomes, avoiding potential bias linked to retrospective studies. However, one limit of our study is to focus only on patients with high grade of glioblastoma, who are known to have a very short life expectancy, with a median expected survival being less than 18 months [37]. Nevertheless, it seems that leukoencephalopathy could appear as soon as within the 6 first months after radiotherapy. Furthermore, the rather large number of included patients will allow us to characterize cognitive defects at short and medium term.

With a better screening and understanding of neurotoxicity, the treatment regiments could be adapted to risk factors present for each patient in order to reduce complication. More, preventive actions and cares could be developed to reduce the burden of cognitive deficits and preserve the quality-of-life and autonomy for patient at risk.

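### The primary endpoint excludes local recurrence without fixing how recurrence and death enter the incidence, covers only local recurrence, and is sized as if every patient were evaluable

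*Protocol article*

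**What the plan says.** In the Protocol article, Study endpoints defines the primary endpoint as "After exclusion of local recurrence, decreased detailed neuropsychological assessment score compared to the" patient's own score before radiotherapy, with a decrease required in at least two cognitive domains.

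Analysis of evaluation criteria carries that definition into the main result: "Based on primary endpoint definition, the estimate of the incidence of cognitive impairment related to radio-induced leukoencephalopathy in our cohort will be made". It names no estimator, denominator or time point. The Cox model in the same section is for dose-response. The Abstract calls the target an incidence rate.

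Sample size consideration plans for a proportion, "with an expected proportion P varying from 0.2 to 0.5", "for a confidence level of 95 %, with alpha risk of 5" %, and concludes that "the number of subjects to be included varies between 246 and 384". It mentions early death only as a reason why "the inclusion of 400 patients will provide good statistical power for this purpose".

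Three other statements bear on the point:
- Procedures says that "tumor response or progression will be assessed by the Response Assessment in Radio-Oncology working group (RANO) Criteria", using the baseline and three-monthly MRI. Formal cognitive assessment is yearly, or earlier if the short computerised test (CSCT) declines.
- Study design sets three years of follow-up per patient. The Discussion describes a population "with a median expected survival being less than 18 months".
- The Discussion also concedes that disease progression can mask the cognitive defect of interest.

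**The concern.** Recurrence happens after baseline. A primary endpoint that begins by excluding it must say what the exclusion does to the patient, and there are at least three possibilities:

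- **Dropped.** The denominator is selected by a later outcome. Recurrence-free time and any decline seen before recurrence are lost, and those who remain are long recurrence-free survivors.
- **Censored.** The estimate is a net risk, in a hypothetical setting without recurrence or death.
- **Recurrence ruled out as the cause.** Nobody leaves the denominator, but recurrence and death still compete with the event, and the result depends on how they are counted.

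These are different quantities, and the choice decides the study's headline figure.

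The word local is a separate problem that arises under every reading. Decline caused by progression away from the original site is not excluded, so it can be counted as radio-induced, although progression is to be assessed by RANO.

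Finally, the planned precision rests on a single proportion in which every included patient yields a result. The document's own survival figure does not support that for assessments out to 36 months.

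**Working it through.** **1. The plan's own figure.** Formula: n = z² P(1 − P) / d², with z = 1.96. The section states no half-width d; d = 0.05 is inferred because it reproduces both figures.
- P = 0.2: 3.8415 × 0.16 / 0.0025 = 245.9, so 246.
- P = 0.5: 3.8415 × 0.25 / 0.0025 = 384.1, so 384.

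The stated range is therefore a plain binomial calculation at ±5 points with everyone evaluable. Including 400 leaves 400 − 384 = 16 patients (4%) above the upper figure.

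**2. Survivors implied by the Discussion.** Assumptions: exponential survival, median at the 18-month bound, time counted from the start of follow-up. S(t) = 0.5^(t/18); half-width = 1.96 √(P(1 − P)/n).

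| Month | S(t) | Alive of 400 | Half-width, P = 0.2 | Half-width, P = 0.5 |
|---|---|---|---|---|
| 0 | 1.000 | 400 | 3.9 points | 4.9 points |
| 12 | 0.630 | 252 | 4.9 | 6.2 |
| 24 | 0.397 | 159 | 6.2 | 7.8 |
| 36 | 0.250 | 100 | 7.8 | 9.8 |

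The half-widths apply to a proportion among those alive at that time. Having 246 or 384 alive at 12 months would need 246/0.630 ≈ 391 or 384/0.630 ≈ 610 inclusions. So 400 just meets the target at the lower end, at the first yearly assessment only.

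**3. Net risk against cumulative incidence, death alone competing.** Assumptions: constant, independent hazards, and a net risk of 40% at 36 months, the middle of the 30 to 50% cited in Background.
- Impairment hazard: −ln(0.6)/36 = 0.0142 per month.
- Death hazard: ln 2/18 = 0.0385 per month.
- Cumulative incidence at 36 months: 0.0142/(0.0142 + 0.0385) × (1 − exp(−36 × 0.0527)) = 0.269 × 0.850 = 0.229.

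Censoring deaths would report 40%, while about 23% of treated patients would develop impairment before dying.

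**4. Adding recurrence, illustration only.** The documents give no recurrence rate. If the median time to recurrence or death were 12 or 9 months (assumed), the same formula gives 18.2% or 15.0%. Under the same independence, keeping only patients alive and recurrence-free at 36 months would still report 40%.

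**5. Scope of the exclusion.** Study endpoints names local recurrence; Procedures assesses progression by RANO; the Discussion says progression can obscure the endpoint. The endpoint is narrower than both the data to be collected and the confounding that the authors acknowledge.

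**The case against.** The strongest reply is that the exclusion phrase is a diagnosis of exclusion: a decline counts once local recurrence has been ruled out as its cause. That fits the Discussion's remark on progression, and Procedures, where the MRI precedes each three-monthly visit. On this reading nobody leaves the denominator and declines before recurrence still count. This stands as a plausible reading. A reader might infer that the plan drops every patient who ever recurs, but no sentence says so.

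A reader might also infer that the result will be reported as a simple proportion. The documents support that for the sample size only. The analysis section names no estimator, the Abstract speaks of a rate, and the Cox model shows that event times are envisaged.

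It is also fair that a condensed article may leave the estimator and censoring rule to the full protocol or analysis plan. Their absence alone is not the point. The point is the wording of the primary endpoint, which later documents inherit.

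Two limits on the numbers stand. The 18-month figure is given for glioblastoma, whereas Table 1 also admits grade III glioma, so survival in the whole cohort could be longer. And some patients who die later will already have had an assessment, so the number alive is not the number who ever contribute a result.

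**Conclusion.** The concern holds in limited form. The primary endpoint builds in a post-baseline event without fixing its effect on the risk set. It covers only local recurrence, so under either reading decline from non-local progression can be counted as radiation injury. The sample size assumes that all patients are evaluable, which conflicts with the survival figure in the same article.

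The best-supported size comes from death alone: at most about 252, 159 and 100 of 400 alive at 12, 24 and 36 months, and an assumed 40% net risk becoming about 23% as actual cumulative incidence. This rests on exponential survival at the 18-month bound, constant independent hazards and the assumed net risk. Conditioning on the future follows only if ever-recurrent patients are dropped, which the documents neither state nor rule out. That recurrence is a dominant competing event is plausible, but it is not quantified in the documents.

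**What to change.** - Keep all included patients in the risk set.
- Replace the exclusion phrase by an event definition: impairment in at least two domains before any RANO progression, at any site. Follow-up for this endpoint ends at first progression or death.
- Estimate cumulative incidence at 12, 24 and 36 months by Aalen-Johansen, with progression and death as competing events. Add a sensitivity analysis for interval censoring, because formal assessments are yearly unless brought forward.
- Use the same end of follow-up in a cause-specific Cox model for dose-response.
- Restate the precision for the chosen quantity and the expected evaluable numbers. For scale, if progression, vital status and impairment were known for all 400, a cumulative incidence of 22.9% would have a half-width of 1.96 √(0.229 × 0.771/400) ≈ 4.1 points. A proportion among 36-month survivors would have 7.8 to 9.8 points.

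The cost is protocol wording and standard software. RANO assessment is already planned; the article does not say that dates of death are recorded, so this must be confirmed. There are two drawbacks. The incidence will look lower than the 30 to 50% cited in Background, and impairment that arises between the last assessment and progression or death is missed.

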**Fig. 1 Fig1:**
[figure not shown]
Study procedure

Every 3 months, once the MRI of the patient is done, a medical visit occurs during which a short cognitive assessment is performed (the CSCT).

Cognitive tests, scales and questionnaires used for the formal assessment are listed in Table 2. An extensive evaluation lasting 2 h is performed with a trained neuropsychologist, followed by self-reported and caregiver-reported scales and questionnaires. The explored domains are intellectual efficiency, general functioning, verbal and visual episodic memory, attention, executive functioning, language, visuospatial and visuoconstructive abilities, mood, fatigue, quality-of-live, subjective complaints and autonomy. The formal assessment occurs at baseline and yearly after radiotherapy. In case of CSCT score decrement during follow-up the next yearly formal assessment is performed earlier. CSCT decrement is defined as a loss of 1 standard deviation compared to baseline (given its low learning-effect and good stability in controls [22]), during two consecutive assessments. The necessity of detecting a decrement during two visits permits to insure that a variation in score is not due to a transitory cause like an infection or fatigue, which is reversible and not linked to leukoencephalopathy. This procedure will allow to study the nature, course and incidence of cognitive decrement following radiotherapy in this population. At baseline and during the follow-up, the CSCT will be compared to the formal cognitive assessment to study its sensibility to detect impairments in this context.

**Table 2 Tab2:** Tests and questionnaires used for the cognitive, mood and behavioral assessment

Domain	Tests, scales and questionnaires
Cognitive assessment	
Intellectual efficiency	National Adult Reading Test (French version) [38]
General functioning	Mini Mental State Examination [39]
	Montreal Cognitive Assessment [40]
	Dementia Rating Scale-2 [41]
Verbal episodic memory	RLRI-16 (Adaptation of the Grober-Buschke test) [42]
Visual episodic memory	Rey-Osterrieth Complex Figure [43]
Executive functions and Attention	Digit Span forward [44]
	Digit Span backward [44]
	Letter-number sequencing [44]
	Categorical and phonetic word fluency [45, 46]
	Trail Making Test [45, 46]
	Computerized Speed Cognitive Test [22]
	Stroop color-word Test [45, 46]
Langage	Boston Naming Test [47]
	Token Test [48]
Visuospatial and visuoconstructive functions	Rey-Osterrieth Complex Figure [43]

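### The primary endpoint sets no minimum size or reliability criterion for cognitive decline, so test-retest noise and practice effects, acting in opposite directions, make the incidence uninterpretable

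*Protocol article*

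**What the plan says.** Study endpoints presents the rule as a definition: "The primary endpoint is the reduction in performance on cognitive tests defined as follows". After exclusion of local recurrence, the criterion is a decreased formal score against the patient's "baseline score before radiotherapy for at least 2 cognitive domains". It attaches no size, reliability criterion, confirmation or practice adjustment to the word for decrease. It also does not say which domains count.

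Analysis of evaluation criteria takes the main result from this rule: "Based on primary endpoint definition, the estimate of the incidence of cognitive impairment related to radio-induced leukoencephalopathy in our cohort will be made".

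Procedures describes what the battery covers: "The explored domains are intellectual efficiency, general functioning, verbal and visual episodic memory, attention, executive functioning, language, visuospatial and visuoconstructive abilities". Table 2 arranges the cognitive tests in seven domain rows and lists the Rey-Osterrieth Complex Figure in two of them (visual episodic memory, and visuospatial and visuoconstructive functions). The battery is given at baseline and then yearly during a 3-year follow-up.

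For the screening test the article does fix a size: "CSCT decrement is defined as a loss of 1 standard deviation compared to baseline", at two consecutive assessments. It explains why: "The necessity of detecting a decrement during two visits permits to insure that a variation in score is not due to a transitory cause".

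On formal testing, the Discussion says that it "cannot be performed as often as needed in this population because of an important learning-effect".

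**The concern.** A score obtained twice from a patient who has not changed will differ by measurement error, and about half of those differences are falls. If any fall counts and only two domains are needed out of five to seven, most such patients could qualify by chance. Repeating the comparison each year against the same baseline adds further chances.

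Repeated exposure to the tests raises later scores. That makes chance falls rarer, but it also conceals real decline. The reported incidence would then be the sum of two opposing errors of unknown size.

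The incidence is the main objective. The follow-up comparison of the CSCT with the formal assessment would inherit the problem. So would the Cox dose-response model, if its cognitive complications are defined by this endpoint.

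**Working it through.** **1. The plan's own figure.** Sample size consideration gives 246 to 384 subjects for an expected proportion P of 0.2 to 0.5 at 95% confidence. The half-width d is not stated; d = 0.05 is inferred because it returns both figures with n = 1.96² × P(1−P) / d²:
- P = 0.2: n = 245.9
- P = 0.5: n = 384.1

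The implied aim is therefore to know the incidence to within about 5 points.

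**2. Noise alone, one visit.** Assumptions: no true change, continuous scores without ties, no practice gain. Each domain then falls with probability 0.5. The number of domains k is taken as 5 to 7, because Table 2 has seven rows and the article does not fix which count.
- Independent changes: P(at least 2 falls) = 1 − (1 + k)/2^k.
- Changes correlated 0.5: the number of falls is uniform on 0 to k, so P = (k − 1)/(k + 1).

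| Domains | Independent | Correlation 0.5 |
|---|---|---|
| 5 | 1 − 6/32 = 81.3% | 4/6 = 66.7% |
| 6 | 1 − 7/64 = 89.1% | 5/7 = 71.4% |
| 7 | 1 − 8/128 = 93.8% | 6/8 = 75.0% |

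If a patient counts on any of three yearly visits, simulation gives 88% to over 99%.

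**3. Effect on the incidence.** Suppose 20% truly decline and all of them are detected. The observed incidence is 0.2 + 0.8 × 0.67 = 0.74 at the low end and 0.2 + 0.8 × 0.94 = 0.95 at the high end.

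**4. Practice gain and ties.** With a gain of g baseline SDs and retest reliability r, one domain falls with probability Φ(−g/√(2(1−r))). The article gives neither g nor r, so r = 0.7 to 0.8 is assumed. For g = 0.5 this is Φ(−0.645) = 0.26 at r = 0.7 and Φ(−0.791) = 0.21 at r = 0.8. Share of unchanged patients classed as cases at one visit, over 5 to 7 domains and correlation 0 to 0.5:

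| Scenario | Share |
|---|---|
| No gain, no ties | 67% to 94% |
| No gain, scores rounded to 0.5 SD | 49% to 81% |
| Gain 0.3 SD, no ties | 44% to 76% |
| Gain 0.5 SD, no ties | 29% to 58% |
| Gain 0.5 SD, scores rounded to 0.5 SD | 12% to 34% |

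With a 0.5 SD gain and no ties, any of three visits gives 53% to 85%. Even the lowest one-visit figure, 12%, adds 0.8 × 12 = 9.6 points to the incidence if 20% truly decline, or 0.5 × 12 = 6 points if 50% do. Both exceed the inferred 5-point half-width, before any allowance for true decline hidden by practice.

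**5. With a per-domain threshold** (no practice gain, one visit, same ranges):
- 1 SD loss: Φ(−1/√(2(1−r))) is 0.098 at r = 0.7 and 0.057 at r = 0.8. False positives are about 3% to 17%.
- Reliable change at z ≤ −1.645: 0.05 per domain. False positives are about 2% to 8%.

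Under the 1 SD rule without confirmation, any of three visits gives about 8% to 36%, so the rule for combining visits matters too.

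**The case against.** The article never says in words that any fall counts. It condenses a fuller protocol, and scoring cut-offs are often left to an analysis plan that is not shown here. A reader might infer that the trial will certainly count any decrease; the document does not establish that. What stands is that the article offers its rule as the definition, ties the incidence to it, and had room to print a cut-off for the screening test. The rule as printed is therefore a fair object of criticism.

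Four further inferences are tempting and are not supported:
- **That the missing practice correction adds to over-classification.** Practice gain raises retest scores, so it lowers false positives and masks decline.
- **That most unchanged patients will be misclassified whatever the conditions.** This holds for noise alone. With a 0.5 SD gain the one-visit share is 29% to 58%, and with ties as well it is below 50% throughout. The article calls the learning effect important but gives no size.
- **That all CSCT accuracy results are compromised.** The baseline comparison sets the CSCT against a formal assessment made at the same time, where no change-from-baseline rule applies.
- **That one Complex Figure score can satisfy two domains.** Table 2 lists the test twice but does not say that the same score feeds both rows.

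It is also fair to say that the 1 SD rule for the CSCT rests on that test's low learning effect and stability in controls. It cannot be carried over to the formal battery on the same grounds.

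**Conclusion.** The point holds. The primary endpoint as printed has no minimum size or reliability criterion, and the incidence rests on it. Noise alone would class about 67% to 94% of unchanged patients as cases at one visit, against an expected 20% to 50%. An assumed practice gain of 0.5 SD brings that to 29% to 58% while hiding true decline. The number of domains, their correlation, the reliability, ties and the practice gain are all assumptions, because the article supplies none of them. The conclusion does not depend on any single value: across the whole range the incidence cannot be read as the frequency of real decline.

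**What to change.** In Study endpoints:
- List the cognitive domains that count and how each is scored.
- Require a minimum decline per domain in at least two of them. A reliable-change cut is preferable (for example z ≤ −1.645), with practice correction where published retest norms exist. Otherwise use a fixed loss (for example 1 SD, naming the reference SD) and state the uncorrected practice effect as a limitation.
- State that one Complex Figure score may not satisfy two domains.
- State whether a decline must be confirmed at a later assessment.

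Report the expected false-positive rate beside the incidence, as a range over the assumed reliability and correlation: about 3% to 17% for 1 SD and 2% to 8% for reliable change, at one visit without practice gain. Say whether the Cox model and the follow-up CSCT comparison use the same definition.

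A fixed SD threshold needs only wording. The reliable-change version depends on external reliability and practice norms, since the article describes no control group and gives no norms. Either version yields fewer events and a lower incidence than the rule as printed.
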